### Initial meeting

3.4

For the two intervention groups, an online meeting will be scheduled (estimated 30–60 min) after the participants receive the device. During the session, the following steps will be checked.•A brief introduction to the study goals and tasks•Request for a verbal consent to proceed with the meeting•Help with setting up and wearing the headband•Downloading and signing into the MUSE app•Tutorials on the assigned practice, and device calibration

The participants are required to complete the pre-intervention questionnaire on the day of the initial meeting.

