### Study procedure

3.2

Participant recruitment occurs through neurology clinics and walk-in clinics in Saskatoon, Canada. The posters will be emailed to individuals who have been referred to the clinics. Once the volunteers email the lab, the initial questionnaire and consent forms will be shared with them. The initial questionnaire includes 45 open-ended and multiple-choice questions (estimated to take 26 min to complete on average) about descriptive information, migraine characteristics and history of the participants as well as their background experience with meditation and whether they believe that meditation could help their migraine headaches. The participants’ history of taking analgesics and acute medications will be assessed based on severity of dependence scale (SDS) [37].

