### Eligibility screening

3.3

All the participants will be screened for eligibility before an invitation is sent to them. To be eligible, the participants should 1. be over 18 years of age, 2. have a diagnosis of chronic migraine from a clinician or have met the criteria for a chronic migraine diagnosis based on ICHD-3 [5], 3. have no frequent background experience of meditation, 4. reside in Saskatoon or be able to receive the device from Saskatoon and the communities nearby, 5. have a smartphone and internet connection for accessing the MUSE app. The exclusion criteria for this study consist of.1.Comorbidity of Raynaud's syndrome or diabetes,2.Plans to start a new preventative migraine treatment.

After checking eligibility criteria, the participants will be randomly allocated in the three arms of the study: the neurofeedback mindfulness, the controlled intervention, and the waitlisted group. The participants will receive an invitation letter with a description of their task, the PDF form of their consent, and the contact information of the researcher in charge of the device delivery.

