**Fig. 1 fig1:**
[figure not shown]
Flowchart for intervention procedure in the study.

The waitlisted group are also required to complete the questionnaires on Week 1, Week 4, Week 8 after being invited to the study and the MUSE device will be delivered to them after completing all three of their questionnaires. In the meantime, they will fill out headache diaries regarding their headache experience. The diaries are accessible via SurveyMonkey and include 24 multiple choice questions (9 min on average) about subjects’ recent headache experience.

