The participants in the attention control group are assigned to have an attention routine in a relaxed position. They are required to sit comfortably and relax in a quiet area to put on their MUSE headband, set it up, and use the same practices on MUSE app but they will mute all the neurofeedback sounds and instructions. Instead, on their smartphone the participants will check their emails, the news, or their preferred social media platform for 10 min. Once the session is over, the participants receive the graphical feedback of their brain activities. The feedback includes a timeline indicating their brain states (active, or relaxed) during the 10-min session.3.The waitlisted group

The participants in this group are informed about being appointed in the waitlisted group and that we will only be collecting headache data from them for 8 weeks. They will complete the questionnaires for three rounds (i.e., Week 1, Week 4, and Week 8) and information about their headaches will be collected via the headache diaries. After 8 weeks, they will receive the MUSE device and will be offered a complementary session on how to use the device for their personal use. A debriefing form will be emailed to all the participants after completion of the study (Fig. 2).

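### The Week 1 baseline is taken after participants know their arm, which can bias the time-by-group comparison, mainly against the waitlist

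*Protocol article*

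**What the plan says.** The protocol article gives the order of events in its Methods.

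- **Before allocation (3.2).** Volunteers receive an initial questionnaire and consent forms. Analgesic history "will be assessed based on severity of dependence scale (SDS"). The other five scales are not listed at this step.
- **Allocation (3.3).** "After checking eligibility criteria, the participants will be randomly allocated in the three arms of the study". Then: "The participants will receive an invitation letter with a description of their task".
- **Device arms (3.4).** "an online meeting will be scheduled (estimated 30–60 min) after the participants receive the device". The agenda includes "Tutorials on the assigned practice, and device calibration". On timing of the scales: "The participants are required to complete the pre-intervention questionnaire on the day of the initial meeting".
- **Waitlist (3.5, 3.6).** "The participants in this group are informed about being appointed in the waitlisted group". They are to "complete the questionnaires on Week 1, Week 4, Week 8 after being invited to the study".
- **Use of the data (3.8, 3.9, 3.11, 3.12).** Participants cannot be blinded. Week 1 is the pre-intervention time point for all six scales. The analysis compares baseline with Weeks 4 and 8 and tests time by group on each scale with repeated measures ANOVA.

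**The concern.** A baseline is a safe reference for a randomised comparison when allocation cannot have influenced it. Here it is recorded after allocation has been disclosed, by people rating their own disability, headache impact, self-efficacy, anxiety, depression and dependence on medication. Receiving a device, or learning that one must wait, could move those answers before any practice begins. The protocol's Introduction itself accepts that expectancy and belief are linked to how headache sufferers report improvement.

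Two things are at stake. First, a shift that differs between arms at Week 1 and later fades appears as a difference in change, which is what the time-by-group test looks for. Second, people who drop out between allocation and Week 1 leave without a baseline on five of the six scales. Only the device arms must receive equipment and attend a meeting in that interval, and section 3.9 expects more attrition in those arms. The analysed groups may then differ from the randomised ones.

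**Working it through.** **Step 1: order of events.**

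| Step | Device arms | Waitlist |
|---|---|---|
| 1 | Initial questionnaire, including SDS (3.2) | Same |
| 2 | Eligibility check, randomisation (3.3) | Same |
| 3 | Letter describing the task (3.3) | Letter; told of waitlisting (3.3, 3.6) |
| 4 | Device delivery, online meeting (3.4) | None |
| 5 | Six scales on the meeting day (3.4) | Six scales at Week 1, counted from invitation (3.5) |

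Disclosure comes before the scales in all three arms. Section 3.4 does not say whether the scales come before or after the tutorial that day, but the letter has already described the task.

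**Step 2: how a shift enters the comparison.** Suppose knowing the allocation moves one arm's score by *s* SD at Week 1, relative to another arm, and a fraction *p* of that shift is still present at follow-up. With no treatment effect, the difference in change is *s·p − s*, so its absolute bias is d = s(1 − p). It equals *s* if the shift has vanished (*p* = 0) and zero if it persists fully (*p* = 1).

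**Step 3: effect on the false-positive rate.** The protocol gives no figure to reproduce here. Inputs:

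- Completers per arm, n: 66/3 = 22 from the stated sample size, or 180 × 0.5/3 = 30 from the allocation target and 50% attrition (3.9, 3.10).
- Correlation between visits, ρ: assumed 0.5 to 0.7.
- Shift *s*: assumed 0.1 to 0.3 SD.

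For a two-arm change-score contrast, in SD units, SE = √(2(1−ρ)) × √(2/n), and the rejection probability is Φ(d/SE − 1.96) + Φ(−d/SE − 1.96).

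Example: n = 22, ρ = 0.5 gives SE = 1 × √(2/22) = 0.302. With d = 0.2, d/SE = 0.663, and Φ(−1.297) + Φ(−2.623) = 0.102.

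| n per arm | ρ | SE | d = 0 | d = 0.1 | d = 0.2 | d = 0.3 |
|---|---|---|---|---|---|---|
| 22 | 0.5 | 0.302 | 5.0% | 6.3% | 10.2% | 16.9% |
| 22 | 0.7 | 0.234 | 5.0% | 7.1% | 13.7% | 25.0% |
| 30 | 0.5 | 0.258 | 5.0% | 6.7% | 12.1% | 21.3% |
| 30 | 0.7 | 0.200 | 5.0% | 7.9% | 17.0% | 32.3% |

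If the shift has vanished, read the column for d = s. If half of a 0.2 SD shift persists, d = 0.1 and the rate is 6.3–7.9%. If all of it persists, d = 0.

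**Step 4: the planned test.** Simulating the 3-arm by 3-visit interaction test, with a 0.2 SD shift in one arm and the same n and ρ, gives about 9–15% if the shift vanishes, 6–7% if half persists and 5% if all persists. The two-arm formula is a fair illustration of the planned analysis.

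**Step 5: time zero.** Section 3.5 counts the waitlist weeks from invitation. Section 3.12 refers to Weeks 4 and 8 of the participants' intervention, while section 3.5 calls the device arms' visits weeks of the study. Counted from the intervention, device-arm visits fall later after randomisation than waitlist visits, by a delivery and scheduling delay that is not given.

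**The case against.** The strongest reply concerns persistence. Participants know their arm at all three visits, so a lasting reporting shift largely cancels in the change score. A reader might infer that any baseline shift passes one-for-one into the result. That holds only if the shift is gone by follow-up, and the documents say nothing about persistence. This stands, so the upper error rates are a worst case.

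A reader might also infer that every change from baseline is compromised. Two facts limit this. The two device arms share the same path (device, meeting, same-day scales), so the contrast between mindfulness and attention control has much less reason to be affected, although their letters describe different tasks and a smaller difference cannot be excluded. The SDS is also collected before allocation.

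A third tempting reading is that the differing time zero is itself a bias from knowing the allocation. It is not: it concerns time since randomisation, and the nominal Week 1 to Week 8 interval is the same in every arm. The wording about invitation may also simply be loose.

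Finally, this is a condensed article and its flowcharts are not shown. That does not remove the point. The text states the order outright, and a statistical analysis plan cannot supply pre-allocation scores that were not collected.

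**Conclusion.** The point holds in a limited form. The Week 1 baseline for all six self-report scales follows randomisation and disclosure of the arm in unblinded participants, and it is the reference for the main comparisons. The time-by-group comparison can therefore be biased, mainly in contrasts with the waitlist, and losses between allocation and Week 1 leave no baseline on five scales.

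The documents establish a risk of bias, not its presence, size or direction. Over the range from full persistence to complete disappearance, an assumed shift of 0.2 SD gives a false-positive rate between 5% and about 17% in the two-arm test. These figures rest on assumed shifts and correlations and on 22 to 30 completers per arm. The inconsistent time zero is a separate, smaller matter of unknown size.

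**What to change.** Administer all six scales with the initial questionnaire, randomise only after they are submitted, and use those scores as baseline in every arm. Keep the meeting-day questionnaire in the device arms only as an additional measure.

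Separately, state one rule for dating Weeks 4 and 8. Moving the baseline ahead of randomisation makes this more important, because the device arms' set-up delay would then lengthen their interval from baseline to follow-up. One option is to schedule waitlist visits with an offset matched to that delay. Follow-up is then comparable without shortening the planned 8 weeks of practice, which could happen if all visits were dated strictly from randomisation.

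Costs: the screening form, now about 26 minutes, grows by up to about 13 minutes (less for the SDS, already asked there) in a population where high attrition is expected. Some screen failures will complete scales that are never used. There will be a short gap between baseline and the start of practice, which the meeting-day questionnaire can describe in the device arms.

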### Intervention follow up

3.5

Except for the waitlisted group, participants will receive daily reminders from a researcher scheduled at 8:00 p.m. They will be required to respond to the researcher by sending “1” for a complete session. All the participants' practices will be monitored daily via MUSE Connect. This platform displays information about the percentage of relaxed or active states and duration of the practice. In case of a pause for more than three days, the researcher will send a follow up with the participant. On Week 4 and Week 8 of the study, the researcher will send participants mid- and post-intervention questionnaires. In the event of having issues with the device, a replacement EEG headband will be scheduled for delivery upon participants’ availability (Fig. 1).

**Fig. 1 fig1:**
[figure not shown]
Flowchart for intervention procedure in the study.

The waitlisted group are also required to complete the questionnaires on Week 1, Week 4, Week 8 after being invited to the study and the MUSE device will be delivered to them after completing all three of their questionnaires. In the meantime, they will fill out headache diaries regarding their headache experience. The diaries are accessible via SurveyMonkey and include 24 multiple choice questions (9 min on average) about subjects’ recent headache experience.

### The assigned tasks

3.6

In this study, the participants will be randomly allocated in three groups of neurofeedback-mindfulness, the controlled intervention, and waitlisted groups. The allocation will be done using stratified randomization to ensure equal distribution (1:1:1) among groups.1.The neurofeedback mindfulness groupThis group is asked to sit comfortably in a quiet area and do one of ten beginner self-guided mindfulness sessions on mind-body scanning techniques from within the MUSE app. Each session includes a brief explanation for 2–3 min before the practice. The participants repeat the same sessions throughout the intervention.1.Introduction to mindfulness: a brief review of mindfulness as a nonjudgmental observation of body and mind.2.Training a puppy: how to monitor emotions and control reactions to different states of mind.3.Sensation of breath: the importance of mindful breathing techniques.4.Counting breaths: how to inhale and exhale properly.5.Sitting comfortably: how to modify positions for mindfulness practices.6.Finding your soundscapes: monitoring the states of mind and how they are associated with the given neurofeedback sounds.7.Dealing with distraction: describing nonreactivity and acceptance of different states of mind.8.Working with discomfort: how to mindfully adjust the states of mind in unfavourable conditions.9.Lowering the bar: Moderating expectations from practices and accept the present state of mind without changing it.10.Bridging to daily life: bringing attention to how the state of acceptance could be conceptualized in everyday routines.

Once the participants start their practices, they receive sounds for their real-time brain activities: thunderstorm for an active state, ocean waves for a neutral state, and birds chirping for a relaxed state. For each 5 s of consistent relaxed state, the participants are reinforced with points.2.The attention control group

The participants in the attention control group are assigned to have an attention routine in a relaxed position. They are required to sit comfortably and relax in a quiet area to put on their MUSE headband, set it up, and use the same practices on MUSE app but they will mute all the neurofeedback sounds and instructions. Instead, on their smartphone the participants will check their emails, the news, or their preferred social media platform for 10 min. Once the session is over, the participants receive the graphical feedback of their brain activities. The feedback includes a timeline indicating their brain states (active, or relaxed) during the 10-min session.3.The waitlisted group

The participants in this group are informed about being appointed in the waitlisted group and that we will only be collecting headache data from them for 8 weeks. They will complete the questionnaires for three rounds (i.e., Week 1, Week 4, and Week 8) and information about their headaches will be collected via the headache diaries. After 8 weeks, they will receive the MUSE device and will be offered a complementary session on how to use the device for their personal use. A debriefing form will be emailed to all the participants after completion of the study (Fig. 2).

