### Participants

3.9

According to A priori G*power software calculation for this study considering both between-subject and within-subject effects, a sample size of 66 is expected to detect significance level of 0.05 with 95 % power through our planned statistical analysis test, i.e., Repeated Measures ANOVA. We aim to look at the effect of time by comparing the baseline with mid-/post intervention reports of the participants for each of the six measurements independently; moreover, we will compare the interaction of time*groups separately for each of our six scales. We will initially allocate 180 participants; yet with reference to the previous studies [22], we could expect up to 50 % of attrition. After applying inclusion and exclusion criteria, participants will be selected for either the meditation, the control, or the waitlisted group. We speculate a higher number of attritions in the meditation and control groups regarding the complexity of the given tasks as compared to the waitlisted group. Fig. 3 provides a flowchart for the number of expected participants at each stage of the study.

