### The instruments

3.11

In this study, six measurements are given to participants at three time points during the study: before the intervention (Week 1), during the intervention (Week 4) and after completing the intervention (Week 8). On average, the total amount of time to complete six questionnaires is estimated around 13 min. These measurements (described in detail below) collect information about migraine disability (MIDAS), headache intensity (HIT-6), headache management self-efficacy (HMSE), anxiety (BAI), depression (CES-D), and severity of dependence on medications (SDS).1Migraine Disability Assessment Scale (MIDAS)

This 5-item instrument focuses on the number of headache-impacted missing days in the migraine population. MIDAS is shown to have significantly high internal consistency scores in United States (Cronbach's α = 0.76) and the UK (Cronbach's α = 0.73) [39].2Headache Impact Test-short form (HIT-6)

This 6-item scale collects information about the intensity of the headache attacks with high reliability of 0.90 Cronbach's ***α*** ([40]). This measurement is a short and sound psychometrical tool to assess how participants evaluate their headache severity.3.Headache Management Self-Efficacy Scale (HMSE)

This measurement is a 25-item scale that measures individuals' perceived level of coping and headache-related disability management with an excellent internal consistency (Cronbach's α = 0.90) [41]. The HMSE score predicts headache-related disability, as shown in MIDAS, regardless of the headache intensity, as usually shown in HIT-6 [41].4BECK Anxiety Inventory (BAI)

This 21-item instrument is a self-report of physical and cognitive symptoms of anxiety on and is validated with a moderate correlation with the revised Hamilton Anxiety Rating Scale (*r* = 0.51)([42]). Internal consistency of this measure is significantly high (Cronbach's α = 0.92) and test-retest reliability in a 1-week period was also acceptable (Cronbach's α = 0.75) [42].5.The Center for Epidemiologic Studies Depression (CES-D)

This validated 20-item scale is a short self-report of the original version with 300 items [43]. The internal consistency of this instrument is high (Cronbach's α = 0.85–0.90) and test re-test reliability is also acceptable (0.45–0.70) [39].6.Severity of Dependence Scale (SDS)

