### Statistical methods

3.12

This protocol is primarily based on comparing the baseline information of the participants with their information on Weeks 4 & 8 of their intervention. With regards to this, we will use Repeated Measures ANOVA for comparing the effect of time on the participants' changes in chronic headache characteristics, psychiatric symptoms, and medicine intake. Additionally, we will compare the interaction effect of time* groups to discover which of the three groups would show most significant changes across time as measured independently for each of the study's scales.

For each of the task-based groups, we will explore the total missed days and attrition at each of the task groups to discover the level of adherence for the two task-based groups. The diaries will also be compared across time to discover how participants manage their headaches via different alternatives and whether there is a change in their trend of headache medicine intake.

Finally, the EEG data analysis will be applied for within-subject and between subject comparisons to determine whether there is a change in adults with chronic migraine's peak alpha frequency over time and during their headache experiences as a function of their practices.

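### Allocation is stratified, but the described Repeated Measures ANOVA names no stratification factor; if the strata predict change over time, the time-by-group test loses some power

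*Protocol article*

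**What the plan says.** Section 3.6 (The assigned tasks) fixes the allocation: "The allocation will be done using stratified randomization to ensure equal distribution (1:1:1) among groups". It does not say which factors define the strata.

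The analysis is described twice. Section 3.12 (Statistical methods) says "we will use Repeated Measures ANOVA for comparing the effect of time on the participants' changes in chronic headache characteristics, psychiatric symptoms, and medicine intake", and adds "we will compare the interaction effect of time* groups to discover which of the three groups would show most significant changes across time". Section 3.9 (Participants) repeats that "we will compare the interaction of time*groups separately for each of our six scales", and ties the sample size to this test: "a sample size of 66 is expected to detect significance level of 0.05 with 95 % power through our planned statistical analysis test". Neither section mentions a stratum or covariate term, and neither expressly rules one out.

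On follow-up, section 3.11 says "six measurements are given to participants at three time points during the study" (Weeks 1, 4 and 8). Section 3.9 says "We will initially allocate 180 participants; yet with reference to the previous studies [22], we could expect up to 50 % of attrition", and about the arms: "We speculate a higher number of attritions in the meditation and control groups".

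**The concern.** Randomising within strata makes the arms more alike on the stratum factor than simple randomisation would. If that factor is related to the quantity being tested and the model omits it, its variance stays in the error term. The standard error of the arm comparison then reflects variation that the design has already removed. The test rejects less often than its nominal 5% and gives up power.

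Hypotheses 2 to 4 depend on this comparison. A second worry is retention. If people leave at different rates by arm, the balance obtained at allocation may not survive among those analysed, and a model without the stratum cannot correct for that.

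**Working it through.** **1. The plan's own figure.** For the within-between interaction with k groups, m times, effect size f, correlation ρ and nonsphericity ε:

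λ = f²·N·m·ε/(1−ρ), df1 = (k−1)(m−1)ε, df2 = (N−k)(m−1)ε.

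Section 3.9 gives N = 66, alpha 0.05 and power 95%, but not f, ρ or ε, so 66 can be matched only under assumptions.
- With f = 0.25, ρ = 0.5, ε = 1, k = 3, m = 3: at N = 66, λ = 0.0625 × 66 × 3/0.5 = 24.75 on 4 and 126 df. Power is 0.986, and N = 54 would be enough.
- N = 66 comes out with the same f and ρ for 3 groups × 2 times, or for 3 × 3 with ε = 0.75.
- For 3 × 3 with ε = 1, N = 66 corresponds to f = 0.31, 0.26, 0.22 or 0.17 at ρ = 0, 0.3, 0.5 or 0.7.

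None of these uses the strata. The sizes carried forward are 66/3 = 22 per arm, and 180 × 0.5 = 90 completers, or 30 per arm.

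**2. Three-time ANOVA with and without the stratum.** Assumptions: 3 groups × 3 times, ρ = 0.5, unit SD of each score, one binary stratum balanced across arms, 20,000 trials per scenario. The SD of Week 1 to Week 8 change within stratum is then √(2 × (1 − 0.5)) = 1. The adjusted model adds stratum and stratum-by-time. The power columns assume that one arm shifts by 0.95 SD by Week 8. Results for time-by-group at N = 66:

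| Stratum effect | Type I error, without | Type I error, with | Power, without | Power, with |
|---|---|---|---|---|
| Level only, 0 to 2 SD | 4.8–5.2% | 4.9–5.3% | 83% | 83% |
| 0.5 SD in change | 4.3% | 4.9% | 82% | 83% |
| 1 SD in change | 2.9% | 4.9% | 77% | 83% |
| 1.5 SD in change | 1.5% | 4.9% | 69% | 83% |

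The first row shows that a stratum effect constant over time leaves with the subject effect. At N = 90, with the treatment shift reduced to 0.8 SD so that power is again about 82%, the pattern is the same (1 SD: 2.9%, and 76% against 82%).

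**3. Change from Week 1 to Week 8 only (2-df group test).** A balanced binary stratum differing by d within-stratum SDs explains (d²/4)/(1 + d²/4) of the change variance. For d = 0.5 that is 0.0625/1.0625 = 5.9%; for d = 1 it is 0.25/1.25 = 20%.
- At 22 per arm without the stratum, type I error is about 4.2% at d = 0.5 and 2.5% at d = 1. About 3 and 10 power points are lost for a shift of 0.8 SD in one arm.
- With the 0.8 SD shift expressed in SDs of total change, power at 22 per arm is 77% against 81% (stratum explains 10%) and 77% against 86% (20%). At 30 per arm it is 90% against 92%, and 91% against 95%. The loss is smaller there because power is nearer its ceiling for the same effect.

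**4. Attrition that differs by stratum and arm.** Assumptions: no true effect, completers 25/25/40 (mindfulness, attention control, waitlist), group test on change. The first column is the assumed share of one stratum among completers in each arm.

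| Share by arm | Type I error unadjusted, 1 SD | Type I error unadjusted, 0.5 SD |
|---|---|---|
| 40/40/50% | 3.3% | 4.6% |
| 32/32/50% | 6.3% | 5.2% |
| 20/20/50% | 15% | 7.9% |

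With the stratum in the model, type I error at 1 SD is 4.9–5.1% in all three rows.

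**The case against.** The strongest reply is that silence is not exclusion. This is a condensed journal article. It names the test and the effects of interest, not a full list of model terms, and covariates are commonly left to a full protocol or SAP that is not shown. For the same reason, not naming the factors is no fault here. This reply stands in large part: nothing shows that the strata will in fact be left out. It does not dispose of the point, because the article describes its model twice and sizes the trial on it, and that model does not mirror the stated allocation.

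A reader might infer that the time-by-group test is conservative and underpowered as planned. The documents do not support that. The loss needs strata that predict change, and no factor is named. The only purpose given for stratifying is equal numbers per arm. The conditions for a large loss are also demanding: explaining 20% of change variance means the strata differ by 2 × √0.20 = 0.89 SD of total change, more than the 0.8 SD treatment shift assumed; 10% means 2 × √0.10 = 0.63 SD.

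A reader might also infer inflated false positives from the expected dropout. The article speculates about attrition by arm only. The 6% and 15% figures need attrition that differs by stratum as well, which is an assumption.

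Finally, Hypotheses 2 and 3 are worded as group differences in scores. In a between-subject comparison of scores, a stratum that affects only level would matter too. The stated group comparison, however, is time-by-group.

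**Conclusion.** The mismatch between stratified allocation and an analysis described without the strata is there in the text. Its consequence is conditional.
- **Strata predict level only:** no material effect on time-by-group.
- **Strata predict change, arms still balanced:** lost power and no extra false positives. At 22 per arm the loss is about 1 to 3 points for a 0.5 SD stratum difference and 6 to 10 points for 1 SD, depending on whether three times or two are analysed. At 30 per arm it is less for a fixed effect.
- **Strata predict change, and attrition differs by stratum across arms:** the unadjusted test can be conservative or liberal, and adjustment brings it back to about 5%.

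These sizes rest on one binary stratum, assumed treatment shifts of 0.8 or 0.95 SD and, for the three-time model, ρ = 0.5. The documents give none of these values. The point is a modest improvement worth making, not a demonstrated error in the planned results.

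**What to change.** In section 3.12, and in the matching description in 3.9, state that the model for each of the six scales includes the factor(s) used to stratify the randomisation and their interaction with time, and that time-by-group is reported from that model. The interaction with time is the term that matters for this test; a stratum main effect alone would not help.

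The cost is one sentence and no new data, since the strata are known at allocation. One binary factor takes the error degrees of freedom for time-by-group from (66 − 3) × 2 = 126 to (66 − 4) × 2 = 124, or from 174 to 172 at 90 completers.
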